### f.4. Sample size estimation

The primary outcome of this study, pain-related function, is measured using the 7-item Brief Pain Inventory (BPI) interference scale. This scale serves as a Multidimensional Pain Interference Index (MPII), providing a comprehensive view of how pain affects various dimensions of an individual's life, including emotional well-being, social interactions, and daily activities. Focusing solely on pain severity may fail to reflect the full impact of pain on a person's overall quality of life. The secondary outcome, pain intensity, is evaluated using the 2-item BPI severity scale. Both BPI scales range from 0 to 10, with higher scores representing worse function or intensity. Understanding the Minimal Clinically Important Differences (MCID) changes in pain interference scores is vital for clinicians to determine whether changes are significant enough to indicate meaningful improvements or declines in quality of life, rather than just being statistically significant. According to previous studies in chronic pain populations, an MCID of approximately 0.7 points for both the BPI interference and severity scales has been identified. However, consensus guidelines have established a 1-point difference as the MCID for both scales, while a 30% reduction from baseline is also recognized as a significant indicator of moderate improvement. In examining the effects of E-PNE with a-tDCS and s-tDCS groups at the final time point (moment 5), which occurs three months post-treatment, a more conservative MCID of 0.6 points was used for estimating the sample size. This cautious approach aims to ensure a thorough evaluation of the study's power to assess the treatment effects. The sample size estimation was performed using the PSS *Health tool* 32. [https://hcupa-unidade-bioestatistica.shinyapps.io/PSS\\_Health/](https://hcupa-unidade-bioestatistica.shinyapps.io/PSS_Health/). To detect a minimum difference of 0.6 points between the means of the Multidimensional Pain Interference Index (MPII) for the a-tDCS group and the s-tDCS group at the final time point (moment 5) in a repeated measures analysis, a sample size of 94 participants (47 per group) was calculated. To account for a potential dropout rate of 15%, the sample size was increased to 112 participants. This calculation was based on an

assumed 80% power, a 5% significance level, and relevant parameters for the treatment group.

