Standard deviation of 1 unit

- Retention rates of 99%, 98%, 96%, and 94% at moments 2, 3, 4, and 5, respectively
- Autoregressive correlation matrix for MPII by BPI of 0.4 for the **a-tDCS** group

For the **s-tDCS** :

- Standard deviation of 1 unit
- Retention rates of 99%, 98%, 96%, and 94% at moments 2, 3, 4, and 5
- Autoregressive correlation parameter of 0.2.

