## Statistical Analysis

Continuous and categorical variables were compared using Fisher's exact test, the chi-square test, and the t-test for independent samples. The Shapiro-Wilk normality test was applied to determine the normal distribution of continuous variables. A Linear Mixed-Effects Regression Models for Repeated Measure (LMM) assessed primary outcomes (pain severity and disability) with treatment, placebo response (responder vs. non-responder), time, and the treatment-by-time interaction as fixed effects, and included a random intercept for patients to account for time differences. If appropriate, we then performed the Bonferroni's Test adjustment for post hoc multiple comparisons to identify differences between the groups at each time point and used a paired t test to assess the effects on each experimental group. The Generalized Linear Model (GLM) was used to examine the treatment effect on the secondary outcomes including quality of life, HPT, PGI-I and the descending pain inhibitory system (DPIS). The treatment effect on primary and secondary outcomes was adjusted for analgesic use and placebo susceptibility. Analgesic use was included in the model to control a potential confounder affecting pain outcomes. This ensures that the observed effects of a-tDCS and s-tDCS are attributable to the interventions rather than variations in analgesic use, thereby enhancing the validity of the results. All analyses were adjusted for multiple comparisons using Bonferroni's Test. The modified ITT (m-ITT) analysis included those completing  $\geq 50\%$  of sessions, with missing data imputed using regression model coefficients. In the m-ITT, with an adjusted protocol, encompassing all patients who completed at least ten sessions. The choice of ten sessions for ITT was guided by most of the literature supporting clinical symptom improvement in chronic pain. This method is not as strict as classical ITT, but it suggests that A-tDCS could be useful in clinical settings with at least a minimum number of sessions. Specifically, we replaced missing values with imputed data derived from a regression model using observed data. The treatment group served as the predictor, and the outcome variable with missing values was imputed based on regression coefficients, indicating the relationship between the treatment group and the outcome. This imputation method was applied, for example, to ten patients who withdrew after ten tDCS sessions. Sensitivity analyses confirmed consistent LMM results with or without imputation ([see per-protocol analysis in results - Supplement II](#)).

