
The standardized difference means (SDM) was used to compute the effect size (ES) by dividing the mean difference between a-tDCS and s-tDCS by the pooled baseline standard deviation (SD). The ES was interpreted as small if lower than 0.20 to 0.49, moderate if between 0.50 and 0.79, and large if larger than 0.80^54. All statistical analyses were performed using two-tailed tests at the 5% significance level with SPSS, version 22.0 (SPSS, Chicago, IL).

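### Missing outcomes in the m-ITT set are filled from a regression on treatment arm alone, which gives the arm mean, understates the standard error and lifts two-sided alpha above the stated 5%

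*Protocol*

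**What the plan says.** The Statistical Analysis section of the protocol defines a modified ITT set of patients with at least half of the sessions, stated as at least ten. Within that set, "we replaced missing values with imputed data derived from a regression model using observed data". The model is then described: "The treatment group served as the predictor, and the outcome variable with missing values was imputed based on regression coefficients". No other predictor is named. The text mentions neither a random residual nor repeated imputations. Its example is ten patients who withdrew after ten sessions.

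The primary model is a linear mixed model with arm, placebo-response class, time and the arm-by-time interaction as fixed effects and a random patient intercept. Secondary outcomes go into a generalized linear model. All inference uses "two-tailed tests at the 5% significance level". The section adds that sensitivity analyses of the mixed model agreed with and without imputation, and refers to a per-protocol analysis in a supplement. The Schedule of assessment table has the BPI at baseline, at weeks 1 to 4 and at three months.

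**The concern.** With arm as the sole predictor, every missing value in an arm receives that arm's observed mean. This leaves the estimated difference at that visit unchanged. It adds records with zero residual, so the estimated variance falls while the apparent sample size rises. Intervals come out too narrow and p-values too small, and the error always runs towards false positives.

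The planned mixed model does not need the step. Fitted to the observed visits, it uses each patient's available scores and is valid when data are missing at random. The fill therefore brings into the main efficacy analysis an error that the chosen model would not otherwise have.

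**Working it through.** **Inputs from the protocol**
- Section f.4: "To detect a minimum difference of 0.6 points between the means" at the final time point; "assumed 80% power, a 5% significance level"; "Standard deviation of 1 unit" in each arm; "Autoregressive correlation matrix for MPII by BPI of 0.4" (a-tDCS) and "Autoregressive correlation parameter of 0.2" (s-tDCS); retention of 99, 98, 96 and 94% at moments 2 to 5; a 15% dropout allowance.
- Section g: 56 patients per arm.
- Statistical Analysis: ten patients as the imputation example, 10/112 = 8.9%.

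**Assumptions, not in the protocol**
- The ten patients split five and five.
- The regression is fitted separately at each visit.
- Values are missing from week 3 onwards.
- The simulated model omits the placebo-response and analgesic covariates.

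**Step 1: the plan's own figure.** The repeated-measures formula is n per arm = (φa + φb)(z0.975 + z0.80)²σ²/δ². Here φ is the last diagonal element of the inverse retention-weighted information: φa = 1.0597 and φb = 1.0629. So n = 2.1226 × 7.849 / 0.36 = 46.28, rounded up to 47 per arm, or 94 in total. For dropout, 47/0.85 = 55.3, rounded up to 56 per arm, or 112. Both stated figures reproduce, so the inputs have been read as intended.

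**Step 2: single-visit two-sample comparison.** After an arm-mean fill,

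reported SE / correct SE = √[n_obs(n_obs − 1) / (n(n − 1))].

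With n_obs = 51 and n = 56 this is √[(51 × 50)/(56 × 55)] = √(2550/3080) = 0.910.

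Actual alpha = 2[1 − Φ(1.96 × 0.910)] = 2[1 − Φ(1.783)] = 7.5%.

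A simulation of 200,000 null trials gave 7.4% with the fill and 5.1% on observed values. With only three per arm imputed (3/56 = 5.4% of patients), it gave 6.3%.

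**Step 3: random-intercept mixed model, last-visit difference.** Six visits, 56 per arm, no true effect, five per arm imputed.
- The mean model SE is 0.184. The true SE is √(2/51) = 0.198. The ratio is 0.93.
- Alpha implied by the ratio: 2[1 − Φ(1.96 × 0.93)] ≈ 6.8%.
- Rejection rates in runs of 2,500 to 4,000 trials were 5.6% to 6.5%. Runs of 20,000 trials gave 6.6% to 7.0%.
- The same model on observed data only, in the shorter runs, rejected in 4.1% to 5.6% of trials, about nominal.
- With three per arm imputed, rejection was 5.4%.

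The random intercept dampens the inflation but does not remove it.

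**The case against.** The strongest reply is that the same section reports consistent mixed-model results with and without imputation, so an analysis close to the remedy has already been run. That stands in part, and it lowers the practical stakes. But agreement in one data set does not make the imputed intervals valid. The supporting analysis is also labelled per-protocol, so it is unclear whether the same patients were compared.

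It is also fair to say that a single fill without residual noise is a reading. The protocol does not use the word single, and it cites a previous trial for the method. The reading follows from values being derived from regression coefficients with arm as the only named predictor.

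Three stronger readings are tempting, but the protocol does not support them:
- **A larger inflation at 15% missing.** The 15% is a planning allowance for dropout. Only patients with at least ten sessions are imputed, and earlier dropouts leave the set. The fraction filled is therefore not 15%.
- **A larger inflation for change from baseline.** Under the plan's autoregressive correlations, a random-intercept model misstates the SE of that contrast even with complete data: model variance is about 1.73 against a true 1.99, so alpha is about 6.8%. The excess cannot all be charged to the imputation.
- **Material bias from ignoring earlier scores.** Under the plan's correlations the preceding visit explains only 0.4² = 16% or 0.2² = 4% of the variance. Baseline correlates 0.4⁴ = 0.0256 or 0.2⁴ = 0.0016 with moment 5. A bias of −0.04 SD appeared only with an assumed correlation of 0.7 and an assumed 8-to-2 dropout split related to the last score. In that scenario the observed-data model was itself off by +0.03 SD. The protocol gives no reasons for withdrawal.

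**Conclusion.** The imputation is wrong as written: it is an arm-mean fill treated as observed data. At ten imputed patients the SE is about 7% too small in the random-intercept model and 9% too small in a single-visit comparison. The corresponding alphas are about 6–7% and about 7.5%, against the stated 5%. The second figure matters only if secondary outcomes were filled the same way, which the text does not settle.

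The inflation is moderate and shrinks with fewer imputed patients. Ten is given as an example, so it need not be the total. The sizes rest on the even split, visit-specific means and the deterministic reading. The case rests on understated uncertainty, not on demonstrated bias. The choice between the m-ITT set and all randomised patients is a separate question.

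**What to change.** Remove the arm-mean fill from the main analysis. State that the planned linear mixed model is fitted by REML to all observed BPI values, and report the imputed version at most as a sensitivity analysis. State also which patients enter the with-imputation and without-imputation comparison.

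For single-visit outcomes, if imputation is kept, use multiple imputation with arm, placebo-response stratum, baseline value and earlier BPI scores, combined by Rubin's rules.

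The cost is revised wording and a re-run. No new data are needed and the required sample size does not change. The last-visit interval widens by about 7% in the ten-patient scenario (model SE 0.197 on observed data against 0.184 with the fill), which is the uncertainty that the fill had hidden.

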### **Secondary Outcomes:**

- ii. The Brief Pain Inventory (BPI) assesses pain at its “worst,” “least,” “average,” and “now” (current pain) on a 0–10 numerical rating scale, where 0 indicates no pain and 10 represents the worst pain imaginable. This assessment was conducted weekly during treatment and three months after treatment completion. These single-item measures are supported by IMMPACT recommendations for pain assessment in clinical trials  and the FDA Draft Guidance for Patient-Reported Outcome Measures .
- iii. The Brazilian Profile of Chronic Pain: Screen (B-PCP) identifies the individual's multidimensional pain experience across three domains: pain severity (0-32), disability (0-36), and emotional burden (0-25). Higher scores indicate

- greater disability or emotional distress, with a total score ranging from 0 to 93 points. Changes from baseline to the end of treatment and at three months follow-up will be analyzed.
- iv. Fibromyalgia Impact Questionnaire (QIF): Measures the impact of fibromyalgia on quality of life across three domains: function (9 questions), overall impact (2 questions), and symptoms (10 questions). Scores are weighted differently, with a maximum total score of 100 .
  - v. Patient Global Impression of Improvement (PGI-I): A 7-point scale assessing patients' perceptions of symptom improvement post-treatment, ranging from "very much worse" (1) to "very much improved" (7) . Impressions were categorized into "improved" or "very much improved" versus "very much worse" to "slightly improved".
  - vi. Quantitative Sensory Testing (QST) is a standardized protocol using a computer Peltier-based device thermode (measuring 30X30mm), which was attached to the skin on the ventral aspect of the mid-forearm. The temperature was set at 32OC and increased at a rate of 1 OC/s until it reached a maximum of 52Oc. Each participant was instructed to push the button when the stimulation became painful. To determine the heat pain threshold, each patient's threshold was measured three times, with a 40-second break between each assessment. The average of the three assessments was used to define the heat pain threshold for each patient .

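### Agreement of the mixed model with and without arm-only imputation says nothing about withdrawals that depend on unseen outcomes, and is near-automatic if the comparator is completers

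*Protocol*

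**What the plan says.** All of this stands in the protocol's Statistical Analysis section unless noted.

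- **Imputation model:** "The treatment group served as the predictor, and the outcome variable with missing values was imputed based on regression coefficients". No other predictor is named, and neither the patient's own history nor a random residual is mentioned.
- **Who was imputed:** "This imputation method was applied, for example, to ten patients who withdrew after ten tDCS sessions". The split by arm is not given.
- **Analysis set:** the modified intention-to-treat set, "encompassing all patients who completed at least ten sessions".
- **The check:** "Sensitivity analyses confirmed consistent LMM results with or without imputation", with the pointer "see per-protocol analysis in results - Supplement II". The section does not say whether the unimputed analysis uses completers only or all available data, and it describes no other missing-data check.
- **Model:** a linear mixed model with treatment, placebo response, time and treatment-by-time, which "included a random intercept for patients to account for time differences". In addition, "The treatment effect on primary and secondary outcomes was adjusted for analgesic use and placebo susceptibility".
- **Data available before withdrawal:** the schedule of assessment lists the BPI at baseline, weeks 1 to 4 and three months. The Secondary Outcomes section says of the BPI pain ratings: "This assessment was conducted weekly during treatment and three months after treatment completion".

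**The concern.** A sensitivity analysis for missing data is useful when it varies the assumption that the data cannot test. Here the imputation appears to add nothing to what the observed patients already show. Comparing it with an analysis that omits the imputed values may then agree by construction.

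The plausible worry in a home-stimulation trial is that patients stop because they do not benefit. If the later outcomes of such patients are worse than those of patients who stayed, and more of them are in the active arm, the reported benefit is too large. A reader who sees the results described as consistent with and without imputation would take this worry to have been addressed.

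**Working it through.** **1. The plan's own design figure.** Inputs from the sample size section: difference 0.6, SD 1 in each arm, AR(1) correlation 0.4 (active) and 0.2 (sham), retention 99, 98, 96 and 94%, two-sided 5%, power 80%. The repeated-measures formula gives 46.3, so 47 per arm and 94 in total. With 15% dropout, 47/0.85 = 55.3, so 56 per arm and 112. The plan's figures reproduce, and 0.6 points and 56 per arm are used below.

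**2. What arm-only imputation does.** Take an arm with n patients, of whom m are missing at a visit, and observed mean ȳ. The regression on arm predicts ȳ for each missing value, so the new arm mean is

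((n − m)·ȳ + m·ȳ)/n = ȳ.

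The arm difference at that visit equals the completers' difference. This assumes visit-by-visit imputation, no covariates, and a per-protocol set that drops exactly the imputed patients.

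**3. Check by simulation.** Settings: 56 per arm, six visits, SD 1, true final difference −0.6, ten patients with nothing observed after week 2, random-intercept model with intraclass correlation 0.4 or 0.7, 200 runs per setting. The correlations and the week-2 cut-off are assumptions. Mean estimates at the final visit (intraclass correlation 0.4 / 0.7):

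| Who withdraws (active/sham) | All available data | Arm-mean imputed | Completers |
|---|---|---|---|
| Random, 5/5 | −0.60 / −0.61 | −0.60 / −0.60 | −0.60 / −0.60 |
| Worst observed scores, 5/5 | −0.61 / −0.61 | −0.61 / −0.62 | −0.61 / −0.62 |
| Worst observed scores, 8/2 | −0.61 / −0.61 | −0.70 / −0.75 | −0.70 / −0.75 |
| Worst observed scores, 10/0 | −0.61 / −0.61 | −0.77 / −0.85 | −0.77 / −0.85 |
| Worst active and best sham, 5/5 | −0.60 / −0.61 | −0.78 / −0.88 | −0.78 / −0.88 |

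Without covariates, imputed and completer estimates were identical to rounding error in every run. With the placebo-response covariate they differed by at most about 0.02. The available-data model differs from both by 0.09 to 0.27 on average when withdrawal depends on observed scores and differs by arm, because earlier scores enter through the random intercept. With the protocol's AR(1) correlations and an intraclass correlation of 0.15 in the fitted model, the gaps are smaller: −0.57 against −0.62 for 8/2, and −0.55 against −0.62 for 10/0.

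**4. Unseen outcomes.** Suppose k active withdrawals are truly d points worse than assumed at the final visit, and sham withdrawals are as assumed. The true difference shrinks by k·d/56:

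| Active/sham split (assumed) | d = 1 | d = 2 | d = 3 |
|---|---|---|---|
| 5/5 | 0.09 | 5·2/56 = 0.18 | 0.27 |
| 8/2 | 0.14 | 8·2/56 = 0.29 | 0.43 |
| 10/0 | 0.18 | 10·2/56 = 0.36 | 0.54 |

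The d-shifted values are never observed and enter none of the three analyses. All three therefore return the same result whatever d is.

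**The case against.** The strongest reply is that the comparison is not empty. A reader might infer from step 2 that the two analyses always give the same estimate, so that the check could never fail. The documents do not support that. The unimputed analysis is not defined. If it is the mixed model on all available data, it needs only that withdrawal be explained by observed history, whereas arm-only imputation needs withdrawal to be unrelated to outcome within arm. The comparison then says something about that gap, as step 3 shows. P-values can also differ when estimates agree: under random withdrawal the imputed standard error was 0.182, against 0.190 to 0.193 with available data.

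Three further objections carry weight.

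- The exact identity is for unadjusted means. The planned model also adjusts for placebo response and analgesic use, and adjustment for analgesic use was not simulated. A per-protocol set may also not drop exactly the imputed patients.
- The sizes in step 4 depend on an unstated arm split and on shifts of 1 to 3 points, which are 1 to 3 of the protocol's assumed SDs, applied to the active arm only.
- The text reports consistency without using the word robust, and a tipping-point analysis could stand in a statistical analysis plan that is not shown. Its absence from the protocol is therefore not the fault raised here.

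What remains is the method and the reassurance that the protocol itself states. None of these replies makes the comparison sensitive to outcomes that nobody observed.

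**Conclusion.** The point holds in a limited form. Agreement with and without this imputation is not evidence that the primary result withstands outcome-dependent withdrawal. If the comparator is completers, agreement of the arm difference is near-automatic: exact without covariates under the assumptions in step 2. If it is the available-data model, the check has some content about withdrawal linked to observed scores, but still none about unobserved outcomes.

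For a 2-point shortfall in active withdrawals, the unseen loss is 0.18, 0.29 or 0.36 of the 0.6-point design effect. This assumes 56 per arm analysed and a 5/5, 8/2 or 10/0 split. The figures illustrate what could go unseen and do not estimate what happened. A reader might go further and conclude that the trial's result is wrong, or that the check passes under every missing-data mechanism. Neither follows: nothing in the protocol shows how the withdrawn patients fared, and step 3 gives mechanisms under which the available-data comparison would show a difference. This should be changed, but it does not by itself overturn the analysis.

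**What to change.** 1. State which analysis is meant by the one without imputation: completers, a defined per-protocol set, or all available data.
2. Do not present agreement between the two as evidence of robustness to missing data.
3. Replace the arm-only single imputation with multiple imputation of BPI interference from arm, placebo stratum and the patient's earlier BPI scores.
4. Add a delta-adjusted (tipping-point) analysis that makes imputed active-arm values worse in steps, for example 0.5, 1.0, 1.5 and 2.0 points, and one run that imputes active withdrawals from the sham arm. Report the delta at which the conclusion at the final time point (moment 5) changes, and judge it against the 1-point minimal clinically important difference cited in the sample size section.
5. Report the withdrawals by arm.

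The cost is a paragraph of text and a few hours of programming on data already collected, with no new patients or procedures. The drawback is that the robustness statement may become less favourable.

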### **Inclusion Criteria**

Women aged 18 to 75 years; right-handed, literate, with a confirmed diagnosis of fibromyalgia (FM) according to the criteria of the American College of Rheumatology (2010-2016). These criteria required assessment using the widespread pain index (WPI) and the symptom severity score (SSS). Specifically, participants needed either a WPI score of at least seven, or a score between 4 and 6 accompanied by an SSS of 9 or higher or widespread pain in four out of five regions along with specific symptoms such as abdominal pain, depression, and headache within the last six months. In general, a combined WPI and SSS score of 13 or more was necessary as per the ACR-2016 standards. Moreover, participants were required to report a minimum score of 6 on the Numerical Pain Scale (NPS), which ranges from 0 to 10, for most days over the previous three months. They also had to agree not to change their doses of antidepressant and anticonvulsant medications during the study.

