### **Primary Outcome**

- i. Pain interference was assessed using a multidimensional pain score from the Brief Pain Inventory (BPI), which evaluates seven daily activities: general activity, walking, work, mood, enjoyment of life, relationships, and sleep. BPI pain interference scores range from 0 to 10, with 0 indicating no interference and 10 indicating complete interference. Overall pain interference was calculated as the mean of the seven items. The assessment was conducted over a 4-week treatment period and at three months of follow-up .

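### The effect-size bands have no lower limit for a small effect and no negligible category, so read literally a standardised difference of 0.00 to 0.19 is labelled small

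*Protocol*

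**What the plan says.** The last paragraph of the protocol's Statistical Analysis section defines the effect size. The SDM is obtained "by dividing the mean difference between a-tDCS and s-tDCS by the pooled baseline standard deviation (SD", and is then put into words by this rule: "The ES was interpreted as small if lower than 0.20 to 0.49, moderate if between 0.50 and 0.79, and large if larger than 0.80". No other category is given. The section does not say whether the bands apply to the absolute value.

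The primary outcome is BPI interference on a 0 to 10 scale (Primary Outcome: "Overall pain interference was calculated as the mean of the seven items"). Section f.4 plans for a difference of 0.6 points with one standard deviation per arm ("Standard deviation of 1 unit"). That gives 47 per group, raised to 112 patients in total for dropout. Section g allocates 56 to each treatment.

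**The concern.** A set of verbal bands should give every possible result exactly one label and should separate an effect too small to mention from a small one. This set does neither. The *small* band joins two incompatible ranges in one phrase, its lower end is open, and the upper band starts above 0.80 although the one beneath it stops at 0.79.

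What is at stake is description. Under the literal rule, a difference indistinguishable from zero is reported as a small effect. The SDM bands are also the only wording rule in the analysis section itself, so a reader of the results would take the label from them.

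**Working it through.** **Inputs.** Bands and denominator: Statistical Analysis. Difference 0.6, SD 1 per arm, retention of 99, 98, 96 and 94% at moments 2 to 5, autoregressive correlations 0.4 and 0.2, 80% power, 5% level, 15% dropout: section f.4. Two-tailed testing: Statistical Analysis. 56 per arm: section g.

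**Step 1: the plan's own figure.** For the repeated-measures comparison at the last moment, n per arm = (z₀.₉₇₅ + z₀.₈₀)² × (φₐ + φᵦ) × SD² / difference², where φ is the variance factor that follows from each correlation matrix and the stated retention. Here φₐ = 1.0597 and φᵦ = 1.0629, so n = 7.849 × 2.1226 × 1 / 0.36 = 46.28. This rounds up to 47 per arm, 94 in total. Then 47 / 0.85 = 55.3, hence 56 per arm and 112 in total. The stated sizes reproduce, so 47 and 56 are used below. The planning effect is 0.6 / 1 = 0.60, which the rule labels *moderate*.

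**Step 2: the rule applied literally.**

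| SDM (absolute) | Label |
|---|---|
| 0.00, 0.10, 0.19 | small |
| 0.20 to 0.49 | small |
| 0.495 | none |
| 0.50 to 0.79 | moderate |
| 0.795 | none |
| 0.80 | none |
| 0.81 | large |

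**Step 3: the possible readings of the first band.**
- Everything up to 0.49: zero counts as small.
- Only values below 0.20: zero counts as small, and 0.20 to 0.49 has no label.
- Only 0.20 to 0.49: values below 0.20 have no label.

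None of the three covers the scale and also keeps a negligible effect apart from a small one.

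**Step 4: how often this would matter with no true effect.** Take the SDM as approximately normal around 0 with SE = √(2/n), assuming equal arms, a visit SD equal to the baseline SD, and no gain from covariates.

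| | 47 per arm | 56 per arm |
|---|---|---|
| SE | √(2/47) = 0.206 | √(2/56) = 0.189 |
| 0.20 / SE | 0.97 | 1.06 |
| P(absolute SDM < 0.20) | 0.67 | 0.71 |
| P(0.20 ≤ absolute SDM < 0.50) | 0.32 | 0.28 |
| P(absolute SDM < 0.50) | 0.985 | 0.992 |

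The literal rule, with the band taken as everything below 0.50, therefore calls a truly null result *small* in about 98 to 99% of trials. A closed 0.20 to 0.49 band would do so in 28 to 32%.

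**The case against.** **The sentence is only garbled.** The protocol is a translation, and the neighbouring bands suggest that 0.20 to 0.49 was intended. That is a plausible repair, but it has to delete words that are there, and it leaves every value below 0.20 without a label. On that reading the 71% is the share of null trials with no label, not the share with a wrong one. The gaps at 0.49 to 0.50 and 0.79 to 0.80 are indeed ordinary two-decimal rounding. The missing label at 0.80 is not: a value that rounds to 0.80 is still not larger than 0.80.

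**The 71% sounds worse than it is.** This stands. It counts both directions, so about 35% of null trials would show a *small* effect in favour of a-tDCS and as many in favour of sham. At 56 per arm, an SDM below 0.20 is less than about 1.06 standard errors from zero and would not be significant at the two-tailed 5% level.

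**Size is also described in points.** This stands in part. Section f.4 cites important differences of 0.7 and 1 point and a 30% reduction, and plans on 0.6, so the SDM bands are not the protocol's only statement about magnitude. The analysis section does not, however, turn any of these into a rule for reading the result.

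**A stronger reading that does not hold.** A reader might infer that the baseline SD also pushes labels upward, because "participants were required to report a minimum score of 6 on the Numerical Pain Scale (NPS" and selection narrows the spread at baseline. The documents do not show this.
- The cut is on a three-month pain-intensity report, not on BPI interference, so any narrowing of the primary outcome is indirect.
- Assume that source-population NPS is normal with mean 5 to 7 and SD 1.5 to 2.5. The SDM is then inflated 1.01 to 1.02 times if interference correlates 0.2 with NPS, 1.06 to 1.11 times at 0.5, and 1.14 to 1.26 times at 0.7. Moving 0.60 to 0.80 needs 0.80 / 0.60 = 1.33 times.
- Narrowing would be more direct for BPI pain severity, which the analysis section also names as primary. Even there, the relevant comparison is with the follow-up SD of the same patients, and the documents give neither a baseline nor a follow-up SD.
- On the single planning SD of 1, the SDM is 0.60 with either denominator.

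A pooled baseline SD is a recognised choice that treatment cannot affect.

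**Conclusion.** The rule is wrong as written and should be corrected. Its first band contradicts itself and has no lower limit, no category exists for a negligible effect, and exactly 0.80 has no label. This follows from the text alone and needs no assumption. The 71% (67% at 47 per arm) rests on the normal approximation in Step 4 and on there being no true effect; it describes mislabelling only under the literal reading.

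The importance is minor. The labels are descriptive, and p-values, the sample size and any success criterion are untouched. It should not be inferred that the labels run too favourable in general: that is established only for values below 0.20 under the literal reading, and not for the choice of denominator.

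**What to change.** Replace the sentence with closed bands on the absolute SDM:
- below 0.20: negligible
- 0.20 to below 0.50: small
- 0.50 to below 0.80: moderate
- 0.80 or more: large

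State the direction of the difference separately, since lower BPI scores are better and the sign depends on the order of subtraction. The pooled baseline SD can stay; an SDM on the SD of the visit is at most an optional companion figure.

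The cost is one sentence, with no new data and no change to any test. The only consequence is that some results that would have been called small will be called negligible.
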